**Independent variables**										
	Recruiting center			✓						
	Sociodemographic variables				✓					
	Basic mental and physical health measures				✓		✓			
	Family environment or place of residence				✓					

### Primary Quantitative Effectiveness Outcomes of the Web App in Monitoring Behavioral Changes

#### End Points

The end points are (1) variables reported every 3 days during 6 weeks within the web app and (2) variables collected in the external software at baseline and every 6 days.

#### Cannabis Use

Cannabis use is determined based on the (1) consumption of cannabis in the last 48 hours (yes or no), reduction of cannabis in the last 48 hours (yes or no), and cannabis abstinence or reduction requiring a cannabis withdrawal test and (2) cannabis product used (hashish, marijuana, etc), mode of administration (smoking, snorting, ingestion, etc), frequency of cannabis use in the last month and week, type of use (alone, accompanied, and both), and reasons for use (addiction, recreational, social, sleeping, etc).

#### Tobacco Use

Tobacco use is determined based on (1) tobacco consumption in the last 48 hours (yes or no) and (2) pattern of tobacco use—type of tobacco products (manufactured cigarettes, roll-your-own, electronic cigarettes, heated tobacco, or similar), frequency of use (daily and occasional), number of units (cigarettes, etc), and nicotine dependence measured using the Heavy Smoking Index (0 to 6), classified as low (0-2), moderate (3-4), and high (5-6) [29,30].

#### Abstinence From Cannabis, Tobacco, and Both

If abstinent of both substances we will ask for a CO measurement test (performed by their clinician and introduced in the software; yes or no).

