## Introduction

### Cannabis and Tobacco Use

Cannabis has emerged as the most widely used illegal drug globally [1]. In Spain, it also holds the status of the most commonly used illegal drug. According to the latest survey conducted in Spain in 2019, 37.5% of adults aged 15-64 years have experimented with cannabis at some point in their lives, with 10.5% reporting usage in the last month (men: 11.4% and women: 4.7%) [2]. Furthermore, approximately 1 in 6 cannabis users develop a cannabis use disorder (CUD) and the odds are increasing to 1 in 2 among daily users [2].

In Western countries, cannabis use is commonly intertwined with tobacco**,** resulting in a significant prevalence of combined usage that continues to rise [3]. For instance, in the United States, the daily use of both substances remained stable over the years from 2005 to 2014, with a usage percentage of 6%. This proportion is higher than that of individuals who consume only cannabis without tobacco, which is around 2% [4]. However, it is important to note that dual cannabis and tobacco use, or co-use, can manifest in various patterns such as (1) concurrent use, where both substances are consumed simultaneously in the form of joints, which is the most prevalent form of cannabis use in Europe [3,5,6]; (2) sequential concurrent use, involving the use of cannabis followed by tobacco or vice versa; (3) asynchronous concurrent use, characterized by cannabis and tobacco usage within the past month but not necessarily during the same instance of consumption; and (4) exclusive cannabis use, where tobacco is not involved [4].

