#### Instruments

##### Gamified Web App

A gamified web app was developed in the first study to prospectively follow-up participants and monitor cannabis and tobacco use, as well as identify withdrawal symptoms (see Table 1). The game of the gamified web app was named DuCATA: Your heroic journey deserves to be told (the original name is “DuCATA: Tu viaje heroico merece ser contado”).

**Table 1 table1:** Variables included in the web app to monitor tobacco and cannabis use.

Frequency	Variable	Description
Every 72 hours	Tobacco use in the last 48 hours	Have you used tobacco in the last 48 hours, with or without cannabis?
Every 72 hours	Cannabis use in the last 48 hours	Have you used cannabis in the last 48 hours?
Every 72 hours	Number of joints	How many joints have you consumed in the last 48 hours?
Every 72 hours	Cannabis reduction	Compared to 2 days ago, have you reduced your cannabis use?
Every 72 hours	Cannabis withdrawal checklist	Have you experienced any of these symptoms in the last 48? Shakiness or tremulousness Depressed mood Decreased appetite Nausea Irritability Sleep difficulty Sweating Craving to smoke marijuana Restlessness Nervousness or anxiety Increased aggression Headaches Stomach pains Strange dreams Increased anger

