#### Statistical Methods

For independent variables, a descriptive analysis will be conducted, including frequencies, percentages, and their 95% CIs. To assess effectiveness measures such as changes in cannabis-tobacco use, withdrawal syndrome, and treatment adherence, frequencies and percentages will be described for baseline and main assessment end points according to the four patterns of cannabis use and they are (1) concurrent, (2) sequential concurrent, (3) asynchronous concurrent, and (4) exclusive cannabis. Incidence rates of abstinence and symptomatology will be calculated for the same assessment end points across the 4 patterns. The RR of quitting or reducing cannabis and tobacco, as well as quit attempts for both substances (95% CI), adjusted for independent variables, and initial consumption pattern, will be calculated using Cox or Poisson robust regression models. Predictive analysis techniques including logistic regression and random forest will be used to model the probability of events occurring based on other factors. Time series analysis will be used to observe consumption trends during the follow-up, and survival analysis of recurring events will be conducted to observe abstinence or reduction processes among participants.

For all analyses, SPSS (IBM Corp) for Windows version 21, Python (version 3; Python Software Foundation), R (version 4.0.3; R Core Team), and scikit-learn will be used. The level of significance will be set at 5% (*P*<.05).

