### Strengths and Limitations

A key strength of our study lies in its methodological rigor, combining qualitative exploration with quantitative measurement. However, the study is limited by its observational nature and the potential for self-report biases in substance use reporting.

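### CO verification is open to some use patterns and closed to others, so pattern comparisons may be biased if CO changes abstinence status; the app's tobacco item also mixes joint tobacco with other tobacco

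*Protocol article*

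**What the plan says.** The section Abstinence From Cannabis, Tobacco, and Both consists of one rule: "If abstinent of both substances we will ask for a CO measurement test". The test is "performed by their clinician and introduced in the software; yes or no". The article gives no cutoff and does not say how a result bears on abstinence status. The yes-or-no field could record that the test was done or what it showed.

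Table 1 (Gamified Web App) puts the same self-report items to every participant every 72 hours. The cannabis item is "Have you used cannabis in the last 48 hours". The tobacco item is "Have you used tobacco in the last 48 hours, with or without cannabis". Joints are counted separately.

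The Introduction (Cannabis and Tobacco Use) defines the two patterns that matter most here: "concurrent use, where both substances are consumed simultaneously in the form of joints", and "exclusive cannabis use, where tobacco is not involved".

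Statistical Methods makes pattern the comparison of interest: "frequencies and percentages will be described for baseline and main assessment end points according to the four patterns of cannabis use". It adds abstinence incidence for the same four groups, and RRs of quitting or reducing adjusted for initial pattern. Objective 3 asks how tobacco use changes during cannabis treatment by typology.

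Strengths and Limitations acknowledges "the potential for self-report biases in substance use reporting" in general terms. It does not mention verification that differs between groups.

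**The concern.** There are two separate problems.

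**Verification.** Whether a claim of cannabis abstinence can be checked depends on current tobacco use, and tobacco use also defines the groups being compared. If failed CO tests turn reported abstainers into non-abstainers, false claims are removed mainly where tobacco is absent and left standing where it continues. Tobacco-using patterns would then appear to do better. Adjusting for initial pattern does not correct an outcome error that itself differs by pattern.

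**The tobacco item.** For someone whose only tobacco is in joints, stopping joints turns both the cannabis and the tobacco answers to no. The tobacco result then carries no information beyond the cannabis result. For someone who replaces joints with cigarettes, the answer stays yes and the change is hidden. Objective 3 is about exactly that kind of change, and the article describes joints as the most prevalent form of cannabis use in Europe.

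**Working it through.** **Who qualifies for a CO test after reporting no cannabis**

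- Exclusive user who stays off tobacco: abstinent of both, always qualifies.
- Concurrent user whose only tobacco was in joints: abstinent of both, qualifies.
- Any user who still smokes tobacco without cannabis: never qualifies.

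Continued tobacco use apart from joints therefore creates the imbalance. The joint wording of the app item does not, because a person truly abstinent from cannabis smokes no joints.

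**Size, if CO changes status.** The article gives no figure to reproduce here. Inputs:

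- p = 0.30, true cannabis abstinence, set equal in both groups. The value matches the background figure in the Introduction for abstinence sustained over the first month of treatment.
- f = 0.05 to 0.20, share of continuing cannabis users who falsely report abstinence (assumed).
- s = 0, 0.5 or 0.9, share of false claims removed among those tested (assumed).
- q = 0.1 to 0.5, share of false claimers in the tobacco-using pattern who also deny tobacco and so are tested (assumed).

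Apparent abstinence:

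- Exclusive: p + (1 − p) × f × (1 − s)
- Tobacco-using: p + (1 − p) × f × (1 − s × q)

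Largest case (f = 0.20, s = 0.9, q = 0.1):

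- Exclusive: 0.30 + 0.70 × 0.20 × 0.10 = 0.314
- Tobacco-using: 0.30 + 0.70 × 0.20 × 0.91 = 0.427
- Spurious RR = 0.427 / 0.314 = 1.36

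Smallest case with s above zero (f = 0.05, s = 0.5, q = 0.5):

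- Exclusive: 0.30 + 0.035 × 0.50 = 0.3175
- Tobacco-using: 0.30 + 0.035 × 0.75 = 0.326
- Spurious RR = 1.03

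Spurious RR, tobacco-using versus exclusive, with no true difference (range over q = 0.5 to 0.1):

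| False claims f | s = 0 | s = 0.5 | s = 0.9 |
|---|---|---|---|
| 5% | 1.00 | 1.03–1.05 | 1.05–1.09 |
| 10% | 1.00 | 1.05–1.09 | 1.10–1.18 |
| 20% | 1.00 | 1.09–1.17 | 1.20–1.36 |

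If every false claimer in both groups is tested (q = 1), the RR is 1.00 whatever s is. The imbalance therefore does harm only when CO results are allowed to alter status.

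**What the tobacco item records when joints stop**

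| Participant | Cannabis item | Pooled tobacco item | Tobacco without cannabis |
|---|---|---|---|
| Tobacco only in joints, stops | yes → no | yes → no | no → no |
| Moves from joints to cigarettes | yes → no | yes → yes | no → yes |
| Joints and cigarettes, keeps cigarettes | yes → no | yes → yes | yes → yes |
| Exclusive cannabis, stops | yes → no | no → no | no → no |

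The first row reads as quitting tobacco, although it restates the cannabis answer. The second and third rows are identical on the pooled item, although one person has taken up separate smoking and the other has not changed. The last row can never count as quitting tobacco.

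**The case against.** The strongest reply on CO is that the article nowhere says a result confirms or overturns self-report. Cannabis and tobacco use are determined from the same reports for everyone, and self-report bias is the stated limitation. This stands. A reader might infer that the pattern comparisons are biased as planned, but the text does not support that. It supports only a conditional statement, because the role of CO and the meaning of the yes-or-no field are left open. The full protocol may settle both.

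The restriction also has a rationale. CO reflects smoke exposure and cannot confirm cannabis abstinence in someone still smoking tobacco. This stands too, and it argues for keeping CO out of the pattern comparison.

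On tobacco, a reader might infer that Objective 3 cannot be answered. That goes too far. The section Tobacco Use also lists product type, frequency, units and nicotine dependence. As printed, Table 2 marks tobacco use pattern and nicotine dependence at baseline and in the 6-day software. A switch to cigarettes should appear there, with a fall in the joint count. The cover is only partial: these data come on a different schedule from the app item, and the article does not say whether tobacco rolled into a joint counts as roll-your-own.

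Nor is counting joint tobacco an error in itself. The item is the same for all patterns, and someone who stops joints and uses no other tobacco really is tobacco-abstinent. The difficulty lies in what the change means and in who is at risk of quitting.

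**Conclusion.** The point holds in conditional form. Eligibility for CO verification depends on the tobacco behaviour that separates the compared patterns; that follows from the text. Bias in the abstinence comparison follows only if CO results change status. Under the assumed rates the spurious RR is then 1.03 to 1.17 when CO removes half of the false claims among those tested, and 1.05 to 1.36 when it removes 90%. It is 1.00 when CO leaves status alone, provided the prospect of a test does not itself change what people report. The planning RR of 1.20 is only a yardstick here, because it was taken from treatment studies and not from a contrast between use patterns.

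The tobacco point does not depend on any assumed rate. On the app's repeated measure, quitting in joint-only tobacco users duplicates the cannabis outcome, and substitution of cigarettes for joints is invisible. Objective 3 can still be addressed in part from the software data. Both issues concern data collection, so later analysis cannot split a pooled answer or recover a test that was never requested.

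**What to change.** 1. State that abstinence in the comparisons across the four patterns is self-reported for everyone, and that CO does not alter it.
2. Keep CO as a secondary check among those reporting abstinence from both substances. Define the yes-or-no field, and report the share tested and the share confirmed by pattern.
3. Split the app's tobacco item into tobacco mixed with cannabis and tobacco without cannabis. Base tobacco change and quitting for Objective 3 on the second. Count quitting among those who use tobacco without cannabis at baseline, and new uptake among those who do not.
4. For participants already enrolled, use the software's product and unit data instead, and say whether rolling tobacco used in joints is included there.

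Cost: some wording on the outcome definition and one extra yes-or-no item in the app. The headline abstinence outcome rests on self-report, a limitation the article already acknowledges. Early participants will lack the split item: 74 were enrolled by June 2024, about half of the 150 anticipated in Results (74/150 = 49%).

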#### Cannabis-Tobacco Users’ Classification

Cannabis-tobacco users will be classified as concurrent use, sequential concurrent use, asynchronous concurrent use, and exclusive cannabis use.

#### ASE Model variables

The ASE model variables are attitudes, subjective norms, and self-efficacy.

#### Attitudes

Motivation to quit was measured on a Likert scale, psychological factors (states of change or readiness to quit cannabis and tobacco and psychological distress) [31]. Psychological distress was measured by using the General Health Questionnaire (GHQ-12) [32].

#### Self-Perceived Health Status

The self-perceived health status will be assessed based on “How would you say your general health is?” (excellent, very good, good, fair, fair, or poor).

#### Self-Efficacy

Self-efficacy is defined as the individual’s confidence to quit cannabis and tobacco [33]. This will be assessed by asking participants, “To what extent do you feel capable of quitting cannabis consumption?” using a Likert scale ranging from 0 to 10 (0= very low to 10= very high).

#### Independent Variables

Sociodemographic variables are (baseline) sex, age, education level, employment status, and occupation. Mental and physical health measures are mental illness presence and comorbidities. Centers are where care is received. The family environment is cohabitation, socioeconomic level, and so forth.

#### Implementation Outcomes

To test the acceptability, appropriateness, and feasibility besides using the qualitative methodology explained, we will quantitatively measure these dimensions among all the participants enrolled in the cohort. We will use the scale developed by Weiner et al [34] that consists of 12 items scored from 1 (completely disagree) to 5 (completely agree). This evaluation will be conducted at the end of the follow-up period (6 weeks), and we will collect this information using a customized questionnaire administered via phone call or text message. Additionally, we will assess other implementation outcomes at the end of study 2 by gathering data on (1) acceptability—the number of individuals who accept or decline to participate in the study; (2) fidelity or adherence—the duration of participants’ usage of the web app, time devoted to playing, number of completed sessions, and so forth; and (3) satisfaction—participants’ opinions about the proposed web app. These variables will be measured using the metadata of the web app (encrypted).

#### Recruitment Procedure

Clinicians verify participant eligibility using a checklist of inclusion and exclusion criteria. They provide oral and written information to potential participants through a leaflet containing study details and information about the study sponsors. Potential participants are informed about the study objectives, procedures, potential risks, benefits, confidentiality measures, and their right to withdraw at any time. This process ensures that only eligible participants who meet the criteria are enrolled in the study.

Additionally, clinicians show a short video explaining the purpose of the research and soliciting participants’ collaboration (available on YouTube [35]). If participants agree to participate, they sign the informed consent and then complete a questionnaire with brief personal information (telephone number, email, name, and national identity document). Subsequently, participants register on the web app and engage with the game daily.

#### Statistical Methods

For independent variables, a descriptive analysis will be conducted, including frequencies, percentages, and their 95% CIs. To assess effectiveness measures such as changes in cannabis-tobacco use, withdrawal syndrome, and treatment adherence, frequencies and percentages will be described for baseline and main assessment end points according to the four patterns of cannabis use and they are (1) concurrent, (2) sequential concurrent, (3) asynchronous concurrent, and (4) exclusive cannabis. Incidence rates of abstinence and symptomatology will be calculated for the same assessment end points across the 4 patterns. The RR of quitting or reducing cannabis and tobacco, as well as quit attempts for both substances (95% CI), adjusted for independent variables, and initial consumption pattern, will be calculated using Cox or Poisson robust regression models. Predictive analysis techniques including logistic regression and random forest will be used to model the probability of events occurring based on other factors. Time series analysis will be used to observe consumption trends during the follow-up, and survival analysis of recurring events will be conducted to observe abstinence or reduction processes among participants.

For all analyses, SPSS (IBM Corp) for Windows version 21, Python (version 3; Python Software Foundation), R (version 4.0.3; R Core Team), and scikit-learn will be used. The level of significance will be set at 5% (*P*<.05).

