Moreover, dual cannabis-tobacco use entails a nuanced description of dependence diagnosis for both substances collectively and individually, alongside the emergence of withdrawal symptoms, particularly when cannabis consumption is reduced or halted [7-9]. Cannabis withdrawal symptoms typically manifest within 2 to 4 days after a reduction or cessation of consumption, peak during the first week, and may persist for up to 4 weeks [10]. The cannabis withdrawal syndrome is recognized and included in the *DSM-5* (*Diagnostic and Statistical Manual of Mental Disorders* [Fifth Edition]) [11]. It is characterized by symptoms such as irritability, anger or aggression, nervousness or anxiety, sleep difficulties (eg, insomnia and disturbing dreams), decreased appetite or weight loss, restlessness, depressed mood, and at least one of the following physical symptoms causing significant discomfort: abdominal pain, shakiness or tremors, sweating, fever, chills, or headache. The symptoms can be assessed using the “Cannabis Withdrawal Checklist” scale. While this scale has been validated [12] and used primarily in English-speaking populations [13-16], its applicability elsewhere warrants consideration.

A meta-analysis has estimated that 47% of cannabis users experience withdrawal syndrome upon cessation, with its occurrence often linked to tobacco use [9]. Additionally, the severity of the cannabis withdrawal syndrome inversely affects the likelihood of successful cessation, with more severe symptoms correlating with lower rates of quitting [9]. Given that cannabis withdrawal syndrome frequently contributes to relapse [17], resulting in modest rates of abstinence maintenance, it is noteworthy that only 30% of individuals who undergo treatment manage to sustain abstinence during the initial month [18]. Various factors contribute to relapse, including the use of other psychoactive substances [19], psychological variables (emotions, social pressure, etc), perceptions of social norms, self-efficacy [20], and sociodemographic variables (sex, age, ethnicity, etc) [16].

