#### Sample Size

According to a recent meta-analysis, the probability of cannabis cessation in this patient population treated using diverse therapeutic approaches is relative risks (RR)=1.48 (28). Given its heterogeneity, we will use a more conservative estimate (RR=1.20). Thus, with an alpha risk of 0.05, a beta risk of 0.20 in a bilateral contrast, and accounting for 20% losses to follow-up, 282 participants will be required. Approximately 2000 people start treatment for cannabis use each year in Catalonia [28], making it feasible to recruit 282 participants within a 1-year period.

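### Time series analysis is a poor fit for consumption trends measured in short panels of about 14 reports per person with expected dropout; a likelihood-based mixed-effects model would suit them better

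*Protocol article*

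**What the plan says.** The Statistical Methods section of the protocol article gives the trend analysis one clause: "Time series analysis will be used to observe consumption trends during the follow-up". It does not say whether the series is individual, averaged over the cohort, or a panel.

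Other sections fix the shape of the data. End Points describes "variables reported every 3 days during 6 weeks within the web app". Table 1 (Gamified Web App) lists the items asked every 72 hours. Use of cannabis, use of tobacco and reduction of cannabis are yes/no items; the one consumption count is "How many joints have you consumed in the last 48 hours". Sample Size plans for attrition, "accounting for 20% losses to follow-up".

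The same Statistical Methods paragraph assigns other questions to other methods: Cox or robust Poisson regression for quitting, reducing and quit attempts; recurrent-event survival analysis for abstinence and reduction; logistic regression and random forest for prediction; frequencies, percentages and incidence rates by use pattern. None of these is a model for the course of a quantity over time, so time series analysis is the only trend method named for number of joints.

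**The concern.** Classical time series methods are built for one series, or a few, observed many times. Here there are many people, each observed a few times, and some stop reporting. Fitted person by person, the method has too few points. Fitted to the average at each report, it describes a group whose membership changes, so a falling average may mean that people cut down or that heavier users stopped reporting.

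The paragraph counts changes in cannabis and tobacco use among its effectiveness measures, so a falling average in a treatment cohort will be read as reduced use. Objective 3 also asks how tobacco use changes by user typology and by level of care. That is a pattern-by-time question, and a single averaged series cannot answer it.

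**Working it through.** **Inputs from the protocol article.** Reporting every 3 days for 6 weeks (End Points); joints over 48 hours, asked every 72 hours (Table 1); 20% loss (Sample Size); 150 participants as the current target (Results), against 282 in Sample Size. The choice between 150 and 282 affects precision, not the direction of the bias.

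**Inputs that are assumed.** Mean joints, between- and within-person spread, and how dropout relates to use. The article gives none of these.

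**Step 1: length of each series.** 6 × 7 = 42 days; 42/3 = 14 scheduled reports per person, fewer for anyone who misses some or leaves. A trend model with first-order autocorrelation has four parameters (level, slope, autocorrelation, variance) to estimate from at most 14 points.

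**Step 2: what dropout does to an average.** Let a fraction f leave, let leavers average d more joints per report than stayers, and let nobody change. If stayers average m, the opening mean is (1 − f)m + f(m + d) = m + fd and the closing mean is m. The artificial fall is f × d. With f = 0.20:

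| d (assumed) | Artificial change |
|---|---|
| 0 | 0 |
| 1 | −0.2 |
| 2 | −0.4 |
| 4 | −0.8 |

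If lighter users leave sooner, d is negative and the average rises, which could hide a real fall.

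**Step 3: simulation with no true average trend.** 150 people, 14 reports, mean 8 joints, between-person SD 3, within-person SD 2, 200 data sets per row. Slopes are joints per report; the mixed model has a random intercept only.

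| Dropout depends on | Residual autocorrelation | Lost | Slope of averages | Mixed-model slope | Mixed-model false positives |
|---|---|---|---|---|---|
| no dropout | 0 | 0% | 0.0004 | 0.0004 | 5.5% |
| previous report | 0 | 19.9% | −0.0536 | 0.0004 | 3.0% |
| previous report | 0.4 | 19.9% | −0.0541 | 0.0030 | 16% |
| no dropout | 0.4 | 0% | −0.0001 | −0.0001 | 18% |
| current, unreported deviation | 0 | 25.8% | −0.0024 | −0.0030 | 6.5% |
| person's own unobserved slope | 0 | 20.3% | −0.0363 | −0.0286 | 58% |

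In the second row the false fall over 13 intervals is 0.0536 × 13 = 0.70 joints. That is 0.70/8 = 8.7% of the mean, or 0.70/√(9 + 4) = 0.19 of the total SD. A first-order autoregressive trend model on the 14 averages, with dropout depending on the previous report, gave slopes of the same size (about −0.054 to −0.057) and P<.05 in 87% of runs. Modelling serial correlation changes the standard error; it does not correct a mean whose composition has shifted.

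**Step 4: a second set of assumptions.** With both SDs equal to 1, heavier users more likely to leave and 18.4% lost, the averaged series fell by 0.178 over 13 intervals, with P<.05 in 55.5% of 200 runs by least squares. A random-intercept mixed model gave −0.027 and 6.5%.

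**The case against.** The strongest reply is that the article names a family of methods and nothing more. A condensed article may leave the unit of analysis, correlation structure and missing-data rule to a fuller plan. Panel or multilevel time series methods exist, and the Introduction frames the data as ecological momentary assessment of individuals. The stated purpose is to observe trends. The 20% is a sample-size allowance, and nothing in the article says heavier users leave sooner. All of this stands, and it limits how firmly the bias can be asserted. It does not make the named method suitable: read in the ordinary way, time series analysis gives either 14 points per person or an average with changing membership, and the paragraph offers nothing else for quantity.

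Three stronger readings are tempting and are not supported.

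- A reader might infer that the plan ignores correlation among one person's reports, so that intervals for pattern comparisons are far too narrow. Modelling serial dependence is what time series methods do. The article nowhere says that reports are pooled as independent, and it assigns pattern comparisons to other methods.
- A reader might infer that all repeated outcomes are mishandled. Abstinence and reduction have recurrent-event and robust Poisson or Cox models; the gap is mainly the trend in number of joints.
- A reader might infer that a mixed model would abolish spurious trends. The last row of the simulation table shows otherwise, partly from informative dropout and partly because that model omits random slopes. With residual autocorrelation of 0.4 and no dropout, a random-intercept model gave 18 to 25% false positives across the runs made.

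**Conclusion.** The point holds in limited form. The method named for consumption trends fits the data poorly, and if it is applied to cohort averages it can report a decline that is only selective loss. The size depends on facts the article does not give. At 20% loss the artificial change is 0.20 joints for each joint by which leavers exceed stayers. In the simulations the false slope ranged from practically zero (no dropout, or dropout on the current unreported deviation) to about −0.057 joints per report (dropout on previous use).

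These figures rest on assumed variances and dropout mechanisms and on a linear model, not the count and binary models the data call for. The quit and reduction estimates from the other models are not in question. The change is worth making because the trend bears on a listed effectiveness measure and the better analysis is cheap.

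**What to change.** Replace the time series sentence, for the trend in number of joints and for the yes/no use items if their trend is reported, with a likelihood-based mixed-effects model using all available reports:

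- negative binomial for joints, logistic for yes/no use;
- fixed effects for time, use pattern and pattern-by-time;
- random person intercepts, with random slopes or a residual autocorrelation structure;
- a stated missing-at-random assumption, and a sensitivity analysis for dropout that depends on unreported use (for example a pattern-mixture shift over a range of values).

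Keep the averaged series as a descriptive plot only, with the number reporting shown at each time point. The recurrent-event, Cox and robust Poisson analyses need no change on this account.

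The cost is an amended sentence and slightly more analysis work; R, already named, can fit these models. The trade-off is a missing-at-random assumption that has to be stated and that the data cannot verify.
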